### Assessment and study outcomes

#### Measurement points

Assessments are carried out at baseline and after 6 weeks (intermediate), 3 months (post-interventional) and 6 months (follow-up). The intermediate assessment after 6 weeks is necessary for mediator analyses that investigate whether a change in symptom severity is mediated via changes in illness-related anxiety and dysfunctional symptom expectations. Except for an additional 12-month follow-up in the SOMACROSS Research Unit, assessment times are identical, allowing for comparison of results. Primary and secondary outcomes and mediator variables will be collected through electronic data entry by patients at home; only the diagnostic interview will be collected via telephone interview. The primary and secondary outcome variables and mediator variables will be measured at each assessment point, and are displayed in Table 1.

**Table 1 tab01:** Outcome instruments of the SOMA.COV study

Outcome variables (assessed via self-report/diagnostic interview)						
Predisposing, triggering and maintaining/aggravating factors	Single constructs	Instrument	Assessment time			
			0 months	6 weeks	3 months	6 months
Primary outcome: somatic symptoms	Overall somatic symptom severity	Patient Health Questionnaire-15 (PHQ-15)	X	X	X	X
Secondary outcomes: symptom-related disability	SARS-CoV-2 infection and Long COVID	Single items	X	X	X	X
	Long COVID symptoms	Patient Health Questionnaire-15 Post-Acute Infection Syndromes (PHQ-15 PAIS)	X	X	X	X
	Fatigue	Fatigue Scale (FS)	X	X	X	X
	Post-exertional malaise	DePaul Symptom Questionnaire Post-Exertional Malaise (DSQ-PEM)	X	X	X	X
	Pain	Pain Disability Index – adapted (PDI)	X	X	X	X
	SOMACROSS core measures^9^	Self-report instruments	X	X	X	X
Diagnosis of somatic symptom disorder (DSM-5)	Diagnostic classification	Structured Clinical Interview for the DSM-5 (SCID-5)	X		X	

Prespecified mediator variables (assessed via self-report)						

Cognitive–perceptual and emotional mechanisms	Illness-related anxiety	Somatic Symptom Disorder – B Criteria Scale (SSD-12)	X	X	X	X
	Treatment expectations	Treatment Expectation Questionnaire (TEX-Q)	X	X	X	X
	Expectation of symptom severity	Numeric Rating Scale (NRS)	X	X	X	X
	Expectation of symptom burden	Numeric Rating Scale (NRS)	X	X	X	X
	Expectation of coping with symptoms	Numeric Rating Scale (NRS)	X	X	X	X

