#### Primary outcome

To test the effect of the expectation management intervention on Long COVID symptoms, the primary outcome for this study is the baseline to post-interventional change in overall somatic symptom severity (3-month follow-up). As harmonised core outcome sets for Long COVID and post-COVID-19 conditions are currently still being developed, overall symptom severity will be assessed with the established PHQ-15,^25^ which is validated in English and German in various diseases and has proven its sensitivity to change as an outcome instrument in many studies.^30^ On a scale of 0 (‘not bothered at all’) to 2 (‘bothered a lot’), the PHQ-15 uses 15 items to measure somatic symptom severity during the past 4 weeks. It includes most of the common Long COVID symptoms and enables us to compare our results to the SOMACROSS Research Unit, which also uses the PHQ-15 as a primary outcome instrument.^9^

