#### Statistical methods

The primary analysis and all prespecified secondary analyses will be conducted in the intention-to-treat sample consisting of all randomised patients with the full analysis set, which is as close as possible to the intention-to-treat population. In secondary analyses, the data of the per-protocol population (subgroup of patients without major protocol violations) will be used and multiple imputation will be applied.

For objective 1, a linear mixed-effects model with the change from baseline for all measured time points will be used to investigate the group differences in the PHQ-15, with treatment group, time and gender as fixed effects, patient as the random effect and baseline PHQ-15 score as the covariate. The interaction between time and treatment group will be tested and excluded from the model if *P* ≥ 0.05. For primary hypothesis, the global treatment effect after 3 months will be considered first. If the two-sided *P*-value is <0.05, the contrasts in change after 3 months for COV.EXPECT versus TAU, COV.SUPPORT versus TAU and COV.EXPECT versus COV.SUPPORT at the 5% level (two-sided hypothesis) will be considered. Because of the closed testing principle, an adjustment of the contrast *P*-values for multiplicity is not necessary.

Secondary end points will be analysed analogously to the primary end point, with the regression model corresponding to the measurement scale (mixed linear model for metric outcomes, mixed logistic model for binary outcomes, cumulative logit model for ordinal outcomes).

In subsidiary analyses, a potential effect of recruitment settings will be investigated by including the setting as a further fixed effect in the analysis. To analyse whether treatment effects on Long COVID resulted through changes in illness-related anxiety or symptom expectations, we will conduct mediation analyses.

To identify further risk factors involved in the persistence of Long COVID (objective 2), we will use longitudinal data from the control group and conduct multivariate regression analyses with symptom persistence as outcome, taking into account the number of predictors and sample size. Patients from the intervention groups will not be included in these analyses because the interventions could bias the results.

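### Dropping the time-by-treatment interaction when P ≥ 0.05 can turn the 3-month primary contrast into an average over 6 weeks, 3 months and 6 months

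*Protocol article*

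**What the plan says.** The Primary outcome section fixes the time point: "the primary outcome for this study is the baseline to post-interventional change in overall somatic symptom severity (3-month follow-up"). Under Measurement points there are three post-baseline visits: "Assessments are carried out at baseline and after 6 weeks (intermediate), 3 months (post-interventional) and 6 months (follow-up"). The caption of Fig. 2 calls the 6-month outcomes secondary and says they played no part in the sample size.

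Under Statistical methods, "a linear mixed-effects model with the change from baseline for all measured time points will be used", "with treatment group, time and gender as fixed effects, patient as the random effect and baseline PHQ-15 score as the covariate". The rule at issue follows: "The interaction between time and treatment group will be tested and excluded from the model" if its P-value is 0.05 or more. For the primary hypothesis, "the global treatment effect after 3 months will be considered first". If that test is significant, the three pairwise contrasts in 3-month change are tested, each at the two-sided 5% level. Secondary end points are to be handled in the same way.

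**The concern.** The two instructions do not fit together. A contrast specific to 3 months exists only while the model lets the treatment effect differ by visit. Once the interaction is removed, nothing in the model belongs to 3 months alone, and the article does not say how a 3-month effect would then be obtained.

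The outcome data therefore decide which quantity is tested. The deciding test has 4 degrees of freedom (three arms, three visits) in a trial sized for one pairwise difference at one visit. A non-significant result from it does not show that the effect is constant. If the effect does vary, the primary estimate, interval and P-value can describe something other than the defined outcome. A real 3-month effect may be diluted, or effects at 6 weeks and 6 months may produce a 3-month claim where there is no 3-month effect.

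**Working it through.** **1. The plan's own figure.** Inputs from Sample size: d = 0.50, two-sided α = 5%, power 80%, 25% loss. A two-sample t-test needs n = 63.77, so 64 per group (power 80.1%). Allowing for loss, 64/0.75 = 85.3, so 86 per group and 3 × 86 = 258. The figure reproduces. It rests on a comparison at 3 months alone.

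**2. What the reduced model estimates.** Let δ₁, δ₂, δ₃ be the COV.EXPECT minus TAU differences at 6 weeks, 3 months and 6 months, in SD units. With complete data and no interaction, the group contrast is (δ₁ + δ₂ + δ₃)/3. Two thirds of the weight lies on visits other than the primary one. Dropout shifts the weights slightly.

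**3. Bias against precision.** With 64 per arm and SD 1, the 3-month contrast has variance 2/64 = 0.03125 (SE 0.177). With correlation ρ between visits, the average has variance 0.03125 × (1 + 2ρ)/3:
- ρ = 0.5: 0.0208, SE 0.144
- ρ = 0.7: 0.0250, SE 0.158

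For the profile 0.25/0.50/0.25 the average is 1.00/3 = 0.33. The shift from 0.50 is 0.167, or 0.167/0.144 = 1.2 standard errors at ρ = 0.5 and 0.167/0.158 = 1.1 at ρ = 0.7. That is large enough to spoil coverage.

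**4. The whole procedure, simulated.** The steps were the 4-df interaction test, removal if P ≥ 0.05, the global test, then COV.EXPECT versus TAU. Assumptions not given in the article: ρ = 0.5–0.7, equal correlation between visits, complete data on 64 per arm, COV.SUPPORT at half the COV.EXPECT effect, and the profiles themselves. Coverage refers to the true 3-month effect. The last column is the rate of significant results for COV.EXPECT versus TAU.

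| True effect at 6 wk / 3 mo / 6 mo | Average | Coverage under the rule | Significant: rule vs interaction kept |
|---|---|---|---|
| 0.50/0.50/0.50 | 0.50 | about 95% | 80–86% vs 70% |
| 0.40/0.50/0.45 | 0.45 | about 94% | 71–79% vs about 70% |
| 0.30/0.50/0.40 | 0.40 | about 90% | not tabulated |
| 0.25/0.50/0.25 | 0.33 | 82–85% | 55–59% vs 70% |
| 0.30/0/0.30 | 0.20 | not tabulated | 9–15% vs about 2% |

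In the third row the mean estimate over all trials is about 0.42–0.43. In the fourth the interaction is dropped in 66–78% of trials. The 70% comparator is below the planned 80% because the contrast must first pass the global test; it is about 75–77% if COV.SUPPORT has no effect.

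**5. How often the term is dropped.** With COV.SUPPORT inert and 64 per arm: 95% for a constant effect, 81% to 70% for 0.3/0.5/0.5, 72% to 54% for 0.25/0.5/0.25, and 34% to 11% for 0.1/0.5/0.5 (ρ = 0.5 to 0.7). With 86 per arm the 0.25/0.5/0.25 figure is 62% to 40%.

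**The case against.** The strongest reply is that the rule often does no harm and can help. If the effect is constant, the average equals the 3-month effect and power rises by about 10–16 points. With mild variation, such as 0.40/0.50/0.45, coverage barely moves and power is no worse. With very large variation the interaction is usually retained. If there is no effect at any visit, the rejection rate for COV.EXPECT versus TAU is 2.6–2.8% under the rule and 2.4% without it, so there is no general inflation of false positives. All of this stands. It does not remove the mismatch between the defined outcome and the reduced model.

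Three stronger readings are tempting, and the documents do not support them:
- **That the 3-month contrast will usually become an average.** The frequency depends on undocumented inputs (step 5), and frequent dropping under a constant effect is harmless.
- **That unequal effects are expected.** The schedule of sessions, booster and follow-up makes them plausible. The article predicts no time course, and it does not say from which point the 3 months to the booster are counted.
- **That the reduced model's standard error is wrong because it ignores the selection.** In the balanced setting simulated, the interaction test is independent of the averaged contrast, so the standard error is valid for the average. The under-coverage comes mainly from the change of estimand.

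A statistical analysis plan is promised and may clarify the 3-month contrast. It cannot be assumed to reverse a rule that the article states outright.

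**Conclusion.** The point holds. The stated rule can replace the 3-month effect with an across-visit average, and it brings secondary 6-month data into the primary test. That the two instructions conflict is algebra and needs no assumption. The size of the harm is conditional: none for a constant effect, negligible for mild variation, moderate for 0.30/0.50/0.40 and substantial for 0.25/0.50/0.25. If the 3-month effect is zero while the other visits show 0.30, the rate of claims rises from about 2% to 9–15%. Nothing in the article indicates which profile is likely. Since the rule can alter the primary estimate, interval and P-value, it should be removed before the analysis is fixed. The sample size calculation is not at fault.

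**What to change.** Delete the exclusion rule. Keep treatment-by-visit in the primary model, with visit as a categorical factor, whatever its P-value. Take the global test and all three contrasts from the model's 3-month estimates. Report the across-visit average only as a labelled secondary result, and apply the same to the secondary end points. A baseline-by-visit term and an unstructured covariance are optional and not needed to cure this problem.

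The change is about one sentence in the protocol, carried into the analysis plan. The cost is the power gained from averaging when the effect truly is constant (about 80–86% against 70% under the assumptions above). That gain is not trivial, but the planned 64 per group and 258 randomised never relied on it. If the sponsor wants it, the average should be declared as the primary quantity in advance, not chosen by a test on the outcome data.

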**Conclusions:**

The study will shed light onto the action mechanisms of a targeted expectation management intervention for Long COVID, which, if proven effective, can be used stand-alone or in the context of broader therapeutic approaches. Further, the study will enable a better understanding of symptom persistence in Long COVID by identifying additional psychological risk factors.

Studies suggest that after an infection with SARS-CoV-2 has abated, a substantial portion of affected patients do not fully recover and may be at risk of persistent somatic symptoms – a phenomenon often described as ‘Long COVID’. There is growing evidence that the development of Long COVID is multifactorial and involves pathophysiological, psychological and social mechanisms.^1^ Among psychological risk factors, increased levels of illness-related anxiety^2–4^ and dysfunctional symptom expectations^5,6^ appear to contribute to processes of symptom persistence after SARS-COV-2 infection. Since both factors can potentially be modified by targeted interventions, this study will investigate a defined mechanism of action: whether Long COVID can be influenced by modifying illness-related anxiety and dysfunctional symptom expectations.

The term Long COVID has become widely used to describe persistent somatic symptoms after a SARS-CoV-2 infection has resolved. Although Long COVID syndrome still lacks specific definition, classification and diagnostic guidelines,^2^ it is thought to comprise symptoms that last >4 weeks after the onset of a SARS-CoV-2 infection, can affect almost every organ system in the body, may change over time and are not better explained by an alternative diagnosis.^7^ According to the UK National Institute for Health and Care Excellence (NICE) COVID-19 guideline and the German Association of the Scientific Medical Societies (AWMF) S1-guideline ‘Post-COVID/Long-COVID’, Long COVID subsumes both ‘ongoing symptomatic COVID-19’^8^ (4–12 weeks after infection) and ‘post-COVID-19 syndrome’ (>12 weeks after infection).^7^ Thus, Long COVID falls under the umbrella term persistent somatic symptoms (PSS), which is used to describe subjectively distressing somatic complaints, irrespective of their aetiology, that are present on most days for at least several weeks.^9^

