#### Sample size

This trial is powered with regard to the difference between intervention 1 (COV.EXPECT + TAU) and the control condition (TAU), as this is the main interest. Because of the closed testing principle, the type one error (alpha) does not need to be adjusted for multiplicity. As there are no comparable trials on Long COVID available, we based our estimation both on our DEPSCREEN-INFO trial (Increasing the Efficiency of Depression-Screening using Patient-Targeted Feedback),^38^ which yielded a between-group effect size of *d* = 0.33 in PHQ-15 scores with an intervention of much lower intensity (written feedback after depression screening), and on the PSY-HEART trial,^27^ which yielded a medium between-group effect size of *d* = 0.71 with an expectation management intervention, but using a different outcome instrument (modified version of the Pain Disability Index). Based on these two studies, we expect a medium effect size (*d* = 0.50) that can be detected with a power of 80%, using a two-sided alpha of 5%, by including 64 patients in each group, resulting in a total sample size of *N* = 192. Based on the results of our previous studies, we assume a loss to follow-up between baseline and the primary outcome measurement (i.e. 3-month follow-up) of 25%, resulting in a total of 258 randomised patients. Assuming that 50% of patients will meet the inclusion criteria, a total of 516 patients will be assessed for eligibility. Figure 2 shows the anticipated flow of participants throughout the trial.

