To compare risk factors and mechanisms of somatic symptom persistence in Long COVID exploratively with those identified in the other conditions investigated in the SOMACROSS Research Unit (objective 3), we will compare the results of the disease-specific regression analyses from the SOMACROSS Research Unit with the derived model from objective 2, and conduct further exploratory analyses.

Subgroup analyses will be conducted on differences in the primary outcome with respect to the following variables of interest: age, gender, education level, social support, duration and severity of Long COVID, any chronic physical disease, any mental health comorbidity, depression and anxiety. For safety analyses, adverse events will be compared between groups and analysed descriptively. Further details of statistical analyses will be described in detail in a statistical analysis plan, which will be finalised before breaking the treatment blind.

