#### Methods against bias

A fixed randomisation list with variable block size and length, stratified by gender, will be generated by an independent member of the biostatistics unit and uploaded into REDCap version 13.7.7 for Windows (REDCap Consortium; see www.projectredcap.org), a software for building and managing online surveys and databases. Assignment will be performed automatically after inclusion in the database. Patient drop-out will be minimised by contacting patients according to a schedule of repeated contact attempts, and by allowing solely written or telephone data collection if electronic collection is not feasible. Because of the electronic collection of outcome variables and having the telephone interviews conducted by trained interviewers who are not involved in the treatment, the study is fully observer-blinded with respect to all treatment conditions. Treating physicians will not be informed about the group allocation or the type of intervention. As in most psychological intervention studies, full patient and therapist blinding is not feasible as their active involvement in the intervention is necessary. Still, patients in the active intervention groups will be blinded. Both interventions will be manualised and therapists and interviewers will be trained and supervised. As a manipulation check regarding potentially overlapping content, contamination and carry-over effects between the two interventions, patients will complete a rating scale on treatment content and on subjective treatment mechanisms after the post-intervention outcome assessment. Potential sampling bias will be avoided by recruiting patients both within and outside of psychotherapeutic care, and by aiming to include both patients with shorter and longer symptom duration in the study. Any questions regarding patient exclusions, serious adverse events and potential study termination will be reviewed by the study's Data Safety and Monitoring Board. Finally, report of the trial and results will follow the Consolidated Standards of Reporting Trials (CONSORT) 2010 recommendations.^39^

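### Baseline symptom duration could be prespecified as a covariate in the primary PHQ-15 model: an optional improvement with a conditional and probably small gain in precision

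*Protocol article*

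**What the plan says.** The Statistical methods section specifies a linear mixed model for PHQ-15 change "with treatment group, time and gender as fixed effects, patient as the random effect and baseline PHQ-15 score as the covariate". Symptom duration is not a term. It appears later in that section, among the variables for subgroup analyses of the primary outcome: "age, gender, education level, social support, duration and severity of Long COVID".

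Under Methods against bias, randomisation is stratified by gender alone, and the sponsor seeks to limit sampling bias "by aiming to include both patients with shorter and longer symptom duration in the study". The introductory text after the abstract defines Long COVID so that "it is thought to comprise symptoms that last >4 weeks after the onset of a SARS-CoV-2 infection", and separates a 4–12 week phase from a phase beyond 12 weeks. The Inclusion criteria adopt the guideline definition and set no upper limit on duration.

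Table 1 lists single items on the infection and Long COVID at month 0. Duration is not named among them, but the subgroup analysis cannot be run without it, so its collection at baseline is a reasonable inference.

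**The concern.** A patient entering in week 5 and one entering after 18 months may have the same baseline PHQ-15 and different prospects. According to the Primary outcome section, the PHQ-15 covers the past 4 weeks, so the week-5 patient's baseline looks back to about week 1. According to Clinical presentation of Long COVID, the illness usually subsides after 2 weeks when mild and within 6 weeks when severe. Part of that baseline score may therefore reflect the acute illness, and the 3-month score would not. Adjusting for baseline PHQ-15 does not separate these two patients.

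If so, some predictable recovery stays in the residual variance of the primary analysis. An uneven split of early entrants between arms would also shift the observed contrast in this one trial, with no prespecified adjustment to remove the shift. The sample size leaves almost no margin above 80% power, so a free gain in precision is worth considering.

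**Working it through.** **Inputs from the Sample size section.** "This trial is powered with regard to the difference between intervention 1" (COV.EXPECT + TAU) and TAU alone; "using a two-sided alpha of 5%, by including 64 patients in each group"; a standardised effect of d = 0.50; power of 80%; 25% loss to the 3-month assessment; 258 randomised. No covariate gain is assumed there.

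**Step 1: reproduce the plan's figure.** A two-sample t-test at two-sided 5% with d = 0.50 needs 63.77 patients per arm for 80% power, which rounds up to 64. Power at 64 per arm is 80.1%. Allowing for 25% loss, 64 / 0.75 = 85.3, which rounds up to 86 per arm, and 3 × 86 = 258. The stated 64, 192 and 258 all reproduce.

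**Step 2: effect of adding duration.** Let R² be the share of residual variance that duration explains once baseline PHQ-15 and gender are in the model. The documents give no value, so the values below are assumptions. The residual SD is multiplied by √(1 − R²), so the effective standardised effect is 0.50 / √(1 − R²), and the equivalent unadjusted sample is 64 / (1 − R²). This treats the 3-month contrast as a single-time-point t-test, as the plan's own calculation does.

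| Assumed R² | Effective d | SE reduction | Power at 64 per arm | Equivalent n per arm |
|---|---|---|---|---|
| 0 | 0.500 | 0% | 80.1% | 64 |
| 2% | 0.505 | 1.0% | 80.9% | 65.3 |
| 5% | 0.513 | 2.5% | 82.1% | 67.4 |
| 10% | 0.527 | 5.1% | 84.1% | 71.1 |

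In terms of the partial correlation r (R² = r²), power is 80.5% at r = 0.1, 81.7% at r = 0.2 and 83.7% at r = 0.3. The gain is below 2 points up to r = 0.2.

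**Step 3: price of the extra term.** One more linear term inflates the variance by about 0.5% at N = 192. The term pays for itself once |r| exceeds roughly √(1/186) = 0.07.

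**Step 4: what R² might be plausible.** Suppose a fraction p of patients are early entrants who improve by δ SD more than the rest in any arm. Then R² ≈ p(1 − p)δ². With p = 10% and δ = 0.5 (both assumed), R² ≈ 0.1 × 0.9 × 0.25 = 0.0225, about 2%. To reach R² = 10% at the same p, δ would have to be √(0.10 / 0.09) = 1.05 SD, more than twice the planned treatment effect.

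**Step 5: chance imbalance.** The SE of a between-arm difference in standardised duration is √(2/64) = 0.177, so a 2-SE imbalance is 0.354 SD. At R² = 5% (r = 0.224) this moves the estimate by 0.354 × 0.224 = 0.08 SD, or 16% of the planned d. At r = 0.3 it moves it by 0.11 SD. This is a fairly extreme draw, and the unadjusted standard error already allows for it.

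**The case against.** The strongest reply is that nothing here is wrong. The model already contains the only stratification factor and the baseline outcome, which is a standard and valid specification. A reader might infer that omitting duration biases the treatment comparison, or that the trial falls short of its stated power. Neither follows. Randomisation protects the contrast on average, its standard error already covers chance imbalance, and the sample size never counted on a covariate gain. Age, depression or anxiety, also on the subgroup list, could be proposed by the same general argument. All of this stands, and it makes the point an optional improvement. The case for duration in particular rests on the recall window and the open-ended entry range.

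A reader might also infer that precision is certainly being lost because recruitment aims for a wide spread. The documents do not support that. Spread helps only if duration is prognostic after adjustment, and no figure is given. The spread is only an aim: the Discussion warns that longer durations may predominate. The infection must be resolved at entry and ICU-treated patients are excluded, so with a 4-week recall the overlap with a mild acute phase of 2 weeks ends at about week 6. The mechanism may therefore concern few patients.

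Two technical objections also stand. If the effect of duration fades over time, one main effect across the 6-week, 3-month and 6-month visits may not capture it fully. In logistic and cumulative-logit models, adding a prognostic covariate changes the conditional effect being estimated, so the change is not purely a gain in precision.

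Deferral to the SAP is only a partial answer, because the article itself lists the covariates of the primary model.

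**Conclusion.** The point holds as an optional, low-cost improvement to the primary PHQ-15 model. The expected gain is about 1 to 4 percentage points of power (80.1% to between 80.9% and 84.1%), or roughly 1 to 7 analysed patients per arm. It rests on an assumed residual R² of 2% to 10%, a figure the documents do not supply. The illustration with 10% early entrants lies at the lower end, and few early entrants would keep it there.

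The plan's analysis is valid without the change, and 64 per arm does deliver the stated power under its own assumptions. The gain would matter most if retention were worse than planned, a risk the Discussion raises. With an assumed 30% loss, 86 × 0.70 ≈ 60 per arm remain and power is 77.5%. Adjusting for duration at R² = 5% would bring it to 79.6%.

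**What to change.** Before the SAP is final, prespecify baseline symptom duration as a fixed effect in the primary PHQ-15 model and in the linear mixed models for metric secondary outcomes. Choose one functional form in advance, for example log weeks since infection, and state how missing self-reported values are handled. Analyse the duration subgroup as a treatment-by-duration interaction added to the same model. Confirm that a baseline item records the duration.

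Do not extend the covariate automatically to the logistic and cumulative-logit models. If it is wanted there, state the conditional effect that is then being estimated.

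The cost is one extra model term (about 0.5% in variance at N = 192), the choice of form, and a rule for missing values. No new data collection should be needed, because the subgroup plan already requires the variable.
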